### Sample size

A power analysis used the standard deviations of mean changes in response/reaction time over a 1-week period for each of the five biomechanical variables obtained in the pilot study. We estimated effect size as a 10 % change of the mean response/reaction time measured at visit 1 for each variable, assuming the control group would have no change. A total sample size of 100 participants, with 50 per group, gives at least 85 % power to detect a 10 % difference in mean change between groups at a 0.05 level of significance. We increased the sample size to 120, with 60 per group, to account for the possibility of up to 15 % loss-to-follow-up.

### Internal quality assurance process

The lead PM conducts an internal quality assurance audit on a quarterly basis for the purpose of maintaining data integrity, ensuring study protocol fidelity and sustaining study operating procedures. During the audit, the lead PM reviews regulatory documentation and Informed Consent Documents. Electronic data is verified by comparing the paper source documents to the data entered into STaRS. Any errors discovered during the quarterly audits are documented, corrected by the site PM, and reported to the site PI, collaborating investigators, and appropriate regulatory bodies if applicable. During these site visits, the lead PM also meets with the site PM, PIs, DCs, and/or clinic command to facilitate communication about overall study status and discuss study timelines, as well as address site concerns or barriers interfering with study conduct. Information gathered during the site visits is conveyed to study coinvestigators. In addition, the PCCR PI has a monthly conference call with the lead PM and onsite PI and PM to monitor study progress.

### Adverse events

For this study, an adverse event (AE) is defined as any untoward medical occurrence that may present itself during the conduct of the study and that may or may not have a causal relationship with the study procedures. AEs are monitored at two levels: (1) a participant self-report AE collected at all visits, and (2) serious adverse events (SAE) regardless of their attribution. Both are reported directly to the site PM, the site PI, and the medical monitor.

There is few rigorously collected data available reporting the risk of AEs following CMT. The lack of quantifiable information is in part the result of the inherent challenges presented by defining and identifying AEs in patients with musculoskeletal complaints with natural symptom variation, the large number of modifiable procedures available to DCs, and the combination of adaptable procedures in varying patient populations [27].

The scientific literature does contain case reports of SAEs such as fractures, serious neurological symptoms, and cauda equina syndrome following CMT. However, case reports are anecdotal in nature and lack definitive causal links. In addition, there are very few case reports of SAEs relative to the total number of chiropractic visits. Therefore, the risk for SAEs following chiropractic care is extremely small and implausible to estimate accurately [28]. The most recent systematic review on this subject failed to identify any reported SAEs resulting from chiropractic care in clinical trials [28].

AEs and the anticipated likelihood of each for this study are included below:Rare but serious (event rate <1 %)Fracture to the ribs or hipNerve injury that may cause loss of bowel or bladder function, lower body sensation or leg paralysisStrokesLess likely (1 % ≤ event rate < 5 %)Inadvertent disclosure of dataLikely (5 % ≤ event rate < 10 %)Some individuals may also experience: neck pain; headache; radicular (radiating) pain; mid-back pain; hands or feet tingling, burning, pricking, or numbness; or dizziness following neck manipulation. These symptoms are usually self-limiting and short-lastingMore likely (event rate ≥10 %)Some participants may experience muscle and/or joint soreness associated with palpation and CMT, particularly at the beginning of the program

Oversight of the reported AEs is conducted by a designated study clinician who reviews a dynamic report of all information submitted by the site PM using the secure web module designed for event reporting for this study. The designated study clinician conveys classification of these events to the site PM for appropriate reporting to the IRBs and other required regulatory bodies. The study clinician may also ask the site PM to contact the participant if more information is needed regarding a reported adverse experience that is potentially serious, related to the study, appears to have no resolution date, or appears to require additional medical follow-up for safety purposes. Our goal is to ensure that we are following up any event that has the potential to affect participant safety and reporting AEs per all study IRB reporting guidelines.

For the second level of AE monitoring, we use the Food and Drug Administration (FDA) definition of a SAE. This is any adverse experience occurring during treatment that results in any of the following outcomes: death, a life-threatening adverse experience, inpatient hospitalization or prolongation of existing hospitalization, a persistent or significant disability/incapacity, or a congenital anomaly/birth defect.

Should any arise, all SAEs and unanticipated problems involving risk to subjects or others are reported to the involved IRBs (Dwight D. Eisenhower Army Medical Center, Palmer Center for Chiropractic Research, and the RAND Corporation), Medical Monitor, DSMC, and the U.S. Army Medical Research and Material Command Office of Research Protections according to the relative reporting guidelines for each entity. The site PM is responsible for reporting all AEs in STaRS and to the lead PM at the PCCR. The lead PM at the PCCR is responsible for ensuring all appropriate parties are informed about any SAEs.

All study protocol violations are reported to the Palmer DSMC. Protocol violations meeting study site’s IRB criteria for reporting are reported per IRB guidelines.

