## Methods

### Overview

This study is a RCT measuring reaction and response times in 120 volunteer SOF personnel at the Blanchfield Army Community Hospital, Fort Campbell, KY, USA. Following a first visit for screening and practicing the five biomechanical tests to be used in assessments, participants are randomly allocated to either a treatment group or to a wait-list control group. Beginning within a week of their first visit, those in the treatment group receive four CMTs over 2 weeks. The first of two assessments consisting of five biomechanical tests is made during their second visit, along with their first CMT. The second assessment is made during their final visit, along with their fourth CMT. In both of those visits with assessments, some of the biomechanical testing is performed before the CMT and some performed after. Participants in the wait-list control group do not receive any treatment but complete the two biomechanical assessments at the same time intervals as those in the treatment group. A flow chart of the study is shown in Fig. 1. Following their involvement in the study, those in the wait-list control group are offered the opportunity to receive four CMTs.

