### Final visit

The final visit of the study is the fifth visit for those in the treatment group and the third visit for those in the wait-list control group. At the beginning of this visit, the participant logs into STaRS and completes the health care utilization and medication-use form and the PROMIS-29 questionnaire, as was also done during visit 1. The five biomechanical tests and CMT/break are conducted in the same manner as at visit 2, which marks the completion of an individual’s participation in the study. Those who are in the wait-list control group are then offered the opportunity to receive CMT. If desired by the participant, the first of four CMTs is given at the final visit of their participation in the study after completion of the biomechanical tests.

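### The SAE definition covers only events during treatment: a narrower window than the AE definition, and one that does not fit the untreated wait-list arm

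*Protocol article*

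**What the plan says.** All the safety wording is in the Adverse events section of the protocol article.

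- An AE is "any untoward medical occurrence that may present itself during the conduct of the study and that may or may not have a causal relationship" (the link meant is to study procedures). The window is the study, and no arm is excluded.
- AEs are monitored at two levels. The first is "a participant self-report AE collected at all visits". The second is "serious adverse events (SAE) regardless of their attribution".
- For that second level, the section gives what it calls the FDA definition: "This is any adverse experience occurring during treatment that results in any of the following outcomes". The serious outcomes follow.

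The arms are described under Overview and Final visit.

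- Treatment arm: "Beginning within a week of their first visit, those in the treatment group receive four CMTs over 2 weeks".
- Wait-list arm: "Participants in the wait-list control group do not receive any treatment but complete the two biomechanical assessments at the same time intervals". If they accept the later offer of manipulation, "the first of four CMTs is given at the final visit of their participation in the study after completion of the biomechanical tests".

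**The concern.** SAEs should be a subset of AEs, observed over the same period and in the same people. Here the SAE rule adds a timing condition that the AE rule lacks, and one randomized arm cannot meet it while on study.

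At stake is how serious events are classified. The study clinician classifies each event, and that classification guides reporting to the ethics boards and other regulatory bodies. If the printed definition is followed, a hospitalization in a treated participant is an SAE, while the same hospitalization in a wait-list participant on the same study day is only an AE. A table of SAEs by arm would then compare a count with a zero fixed by definition. The section itself says that rigorous data on harms after manipulation are scarce and that case reports lack definitive causal links, so a distorted randomized comparison would be a real, if small, loss.

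**Working it through.** The protocol gives no figure to reproduce. The check sets the passages side by side and counts who and what falls outside the SAE window.

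**1. The two windows**

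| | AE definition | SAE definition |
|---|---|---|
| Timing | conduct of the study | during treatment |
| Cause | any | any (attribution disregarded) |
| Arm | not restricted | restricted only through the word treatment |

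The rows for timing and arm differ. The row for cause does not.

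**2. What treatment means in this article.** The Abstract and the Overview both use the word for manipulation and say that the wait-list group has none. The Final visit section places the optional manipulation after the last tests, when participation is complete. In the article's own vocabulary, a wait-list participant has no time under treatment while on study.

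**3. Share of the sample affected.** The Sample size section gives 60 per group and 120 in total: 60 / 120 = 50%.

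**4. Treatment arm before the first manipulation.** Visit 2, with the first manipulation, is booked within a week of visit 1, so up to 7 days fall before treatment. The Sequence of biomechanical testing section puts the final visit 10 days after visit 2; the Overview gives 2 weeks for the course. Taking treatment as the whole course, and visit 2 on the last permitted day:

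- 10-day course: 7 / (7 + 10) = 7 / 17 = 41% of participation lies outside the SAE window.
- 14-day course: 7 / (7 + 14) = 7 / 21 = 33%.

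These are upper values. An earlier visit 2 gives less.

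**5. What the SAE label changes.**

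- *Medical monitor:* both monitoring levels go to this role, so the label is not needed.
- *Data and Safety Monitoring Committee:* its own section has it evaluate the data when any AE occurs, so the label is not needed.
- *Database and clinician review:* all AEs are entered in STaRS and reviewed, so the label is not needed.
- *Ethics boards:* SAEs and unanticipated problems are reported to all three. Other AEs go only as each board's guidelines require, so the label matters in part.
- *Army research-protection office:* named as a recipient of SAEs and unanticipated problems, so the label matters unless the event also qualifies as an unanticipated problem.
- *Any SAE count by arm:* depends on the label entirely.

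**The case against.** **Capture is not at risk.** A reader might infer that serious wait-list events go unseen, or that the SAE label alone decides what reaches the medical monitor and the monitoring committee. The text does not support either inference: AE collection has no arm restriction, all AEs go into STaRS, and both recipients have a route that does not depend on the label. This stands, and it confines the point to classification and reporting.

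**Attribution is not contradicted.** A reader might set the treatment restriction against the statement that SAEs are monitored whatever their cause. One concerns timing and the other causality, so an event during treatment can count whatever caused it. The study-wide window is also stated for AEs and only carried over to SAEs, as the second level of AE monitoring. This stands too: the conflict is between windows.

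**The window is not minutes long.** One could multiply four sessions by the 10 minutes given as typical for a manipulation and get 40 minutes. The 10 minutes is there to set the control group's break, and the Overview describes a course spread over 2 weeks. The course is the natural reading and includes the days between sessions.

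**The wording may be loose.** The sentence is offered as the FDA definition in a condensed article, the fuller protocol is not shown, and no passage excludes wait-list participants from SAE monitoring. Staff may well have applied it to everyone. That is possible, but the printed sentence is the only definition given, and the article otherwise uses treatment to separate the arms.

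**A control SAE rate would be imprecise.** With zero events in 60 controls, the one-sided 95% upper bound is 1 − 0.05^(1/60) = 4.9%, whereas the protocol expects its listed serious events in under 1%. The Statistical methods section plans no comparison of SAEs between arms. This limits the harm, but does not justify different definitions in the two arms.

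**A common window adds no follow-up after the fourth manipulation**, which is given at the final visit. That is correct. The fix makes the arms consistent and does not claim to catch later events.

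**Conclusion.** The point holds as an inconsistency between the AE and SAE definitions. Taken literally, the SAE definition leaves 60 of 120 participants with no qualifying time on study. It also leaves out the treated arm's interval before the first manipulation, at most 7 days, or about a third to two fifths of the nominal schedule at its longest.

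The consequence is SAE classification and reporting that can differ between arms. It does not extend to lost safety data, and nothing in the efficacy analysis, power or type I error depends on it.

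The conclusion assumes that treatment means manipulation, as elsewhere in the article, and that the clinician applies the definition as printed. If site practice already used study participation as the window, only the wording is at fault. Expected SAE numbers are small. The change is still worth making, because it is cheap and the present rule makes an SAE count by arm uninterpretable if followed.

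**What to change.** Reconcile the two definitions in the Adverse events section. Replace the restriction to treatment with one study-participation window that applies equally to both randomized groups, for example: any adverse experience from consent to the end of the participant's final study visit, in either group and whatever its cause, with one of the listed outcomes. State whether the optional manipulation offered to the wait-list group after the final tests lies inside or outside that window.

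The Trial status section says that data collection is complete. In practice this means checking the AEs already in STaRS against the common window, correcting any classification that relied on the narrower wording, and reporting SAEs by randomized arm. Allocation takes place between visits 1 and 2, so events before it should be identified as such in that table.

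The cost is one sentence and a review of existing records, with no added visits or data collection. The downside is that slightly more events may be labelled and reported as SAEs, possibly with late reports to the bodies concerned.

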### Study limitations

One limitation of this study is the use of a wait-list control group for comparison to the treatment group rather than a sham treatment group. A sham treatment would maximize the ability to compensate for the possibility of a placebo effect in the treatment group. However, it is very difficult to provide a sham treatment for HVLA active treatment, so the members of a sham group would likely suspect that they are not receiving an active treatment [29]. Furthermore, the outcome measures used in this study are objective in nature, potentially minimizing any placebo effect.

A limitation inherent in any study involving manual therapies is the variability of the treatment provided for each patient, and even each treatment of each patient. There are so many variables associated with virtually any form of manual therapy that it is impractical to try to quantify them. This is partly due to the fact that each patient’s condition is certainly not constant from one visit to the next, and consequently the manual therapy given is typically modified by the treating clinician to address the specific needs of the patient during any particular visit. This study is intended to investigate the effects of actual clinical practice and, therefore, no attempt was made to restrict the manner in which the clinicians provide their treatment to participants of the study.

Similarly, despite the requirement for participants to meet the inclusion criteria established for the study, there will still be considerable variations within the exact physical condition, some of which are likely associated with age, of the participants in the study. This is also an inherent limitation in studies involving human participants.

Another limitation of the study involves blinding. Due to the setup for this study, it is not logistically feasible for the person administering the assessment tests to be blinded as to which group (treatment or wait-list control) each participant is in. Consequently, there is a possibility that the assessor’s actions toward members of the treatment group might be somewhat more positive or encouraging than their actions toward members of the wait-list control group. This risk is minimized by having scripted dialog and prerecorded video presentations to explain how each assessment test is to be done. The objective nature of all five of the assessment tests reduces the ability for observer bias to impact the results of the tests.

One other limitation of the study is the low number of CMTs being given to each participant. It is currently unknown if CMTs of any quantity would induce a discernable reduction in the reaction time of SOF personnel. Three or four CMTs were chosen as feasible for busy SOF personnel to receive.

## Discussion

SOF personnel as a group are likely to be in need of reaction and response times that are as quick as possible during the course of their assigned duties. One goal of CMT is to maximize the integration and function of the neuromusculoskeletal systems. Therefore, this intervention is well-suited for attempting to optimize the capacity of the numerous components involved in the production of a minimal reaction and response time. This study is designed to show if CMT will result in quicker reaction and response times for those SOF personnel who receive it. The results of the study will be published following completion of data collection and analysis.

Two different random but set sequences of prompts for each of the five biomechanical tests were used to prevent participants from memorizing the sequence and anticipating prompts. However, different sequences can have different levels of difficulty. Consequently, whenever the results of two replications of the same test are to be compared with each other we wanted to have the same sequence of prompts used for those replications of that test. The only replications of each test that are to be used in the data analysis of this study are the ones taken immediately before and after the participant receives a CMT/break. Therefore, for visit 2 and the final visit, the order of prompt sequences and the CMT/break that is used is B, A, CMT/break, A. Having a replication of the test completed using sequence B just before the one with data that will be analyzed that uses sequence A has a double value. Not only does it prevent memorization of the prompt sequence, but it also provides an opportunity for the participant to get in the mode of doing that particular test after doing other, different tests before doing it for analysis.

Once the resulting manuscripts have been published, datasets will be provided for public access. Potential investigators can contact one of the co-PIs to present their hypothesis, study design, instruments and/or data on which to focus, and resources required. Depending upon the needs and desires of the requesting party, the data that is shared may include analytic tables or deidentified or limited datasets that are transmitted to the requesting parties for additional analyses. In addition, the trial is registered on ClinicalTrials.gov, making all key information about the trial freely available.

### Trial status

The first participant was enrolled on 30 September 2014. Data collection for the last of 120 participants was completed on 7 June 2016.

### Trial registration

The RCT discussed in this article was registered on ClinicalTrials.gov with the NCT02168153. The initial version sent to ClinicalTrials.gov was received on 12 June 2014.

## Abbreviations

ACT 2: Assessment of Chiropractic Treatment, part 2
AE: Adverse event
CMT: Chiropractic manipulative therapy
DC: Doctor of chiropractic
DSMC: Data and Safety Monitoring Committee
HVLA: High-velocity low-amplitude
IRB: Institutional Review Board
LBP: Low back pain
PCCR: Palmer Center for Chiropractic Research
PM: Project manager
PROMIS: Patient Reported Outcomes Measurement Information System
RCT: Randomized controlled trial
SAE: Serious adverse event
SOF: special operation forces
STaRS: Submission Tracking and Reporting System
